## Abstract

**Background:**

Despite high quality stroke care, decreased sensorimotor function, anxiety and pain often remain one year after stroke which can lead to impaired health and dependence, as well as higher healthcare costs. Touch massage (TM) has been proven to decrease anxiety and pain, and improve quality of health in other conditions of reduced health, where reduced anxiety seems to be the most pronounced benefit. Thus there are reasons to believe that TM may also reduce anxiety and pain, and improve quality of life after stroke. Further, several studies indicate that somatosensory stimulation can increase sensorimotor function, and it seems feasible to believe that TM could increase independence after stroke. In this study we will evaluate effects of TM after stroke compared to sham treatment.

**Methods:**

This is a prospective randomized open-labelled control trial with blinded evaluation (PROBE-design). Fifty patients with stroke admitted to stroke units will be randomized (1:1) to either a TM intervention or a non-active transcutaneous electrical nerve stimulation (non-TENS) control group. Ten sessions of 30 min treatments (TM or control) will be administered during two weeks. Assessment of status according to the International Classification of Functioning, Disability and Health (ICF), including body function, activity, and participation. Assessment of body function will include anxiety, pain, and stress response (heart rate variability and salivary cortisol), where anxiety is the primary outcome. Activity will be assessed by means of sensorimotor function and disability, and participation by means of health-related quality of life. Assessments will be made at baseline, after one week of treatment, after two weeks of treatment, and finally a follow-up after two months. The trial has been approved by the Regional Ethical Review Board.

**Discussion:**

TM seems to decrease anxiety and pain, increase health-related quality of life, and improve sensorimotor functions after stroke, but the field is largely unexplored. Considering the documented pleasant effects of massage in general, absence of reported adverse effects, and potential effects in relation to stroke, it is essential to evaluate effects of TM during the sub-acute phase after stroke. The results of this project will hopefully provide important knowledge for evidence-based care.

**Trial registration:**

ClinicalTrials.gov: NTC01883947

## Background

In Sweden, about 25,000 individuals suffer a stroke each year. Despite high quality stroke care in Sweden, decreased sensorimotor function, anxiety and pain often remain one year after stroke which may lead to impaired health and dependence, as well as to higher healthcare costs. It is therefore urgent to find new rehabilitation strategies. Touch massage (TM) is a massage treatment consisting of slow strokes with gentle pressure [1]. Although research indicates positive effects of TM on the wellbeing of healthy individuals and patients with ill-health conditions, no study has evaluated TM after stroke. Health is influenced in many ways after stroke, and in this study we focus on health components included in the International Classification of Functioning, Disability and Health (ICF) [2].

One component of ICF is Body Function and we focus in this study on anxiety, pain, and stress reactions. Concerning anxiety, about 50 % of stroke survivors experience anxiety in the acute stage of stroke [3]. In a Cochrane review [4], the authors concluded that there is insufficient evidence to make recommendations about treatment, and that more studies are needed. Our research group found that anxiety could be decreased following administration of TM in other ill-health conditions [1], a conclusion that has been confirmed in other studies (eg. [5–7]). In addition, using fMRI [8] we found increased neural activity in brain regions associated with feelings of pleasure and emotional regulation [9]. Headache, shoulder pain in the paretic shoulder, joint pain, and central post-stroke pain are common after stroke [10]. In earlier studies, our group found that TM can decrease the experience of pain [11], which is in line with results from other studies [12, 13]. To our knowledge, there is only one study [14] that has found an amelioration of pain and anxiety after slow back massage among patients with stroke in a rehabilitation unit. There are therefore good reasons to further explore this issue.

Stress reactions are common in patients suffering from stroke, and it is suggested that massage decreases the stress response and induces relaxation. The physiological mechanism, though, is not fully understood and contradictory results are reported. In a previous study, our research group did not find any significant changes in stress outcomes after TM (blood pressure, cortisol) [1], which may have been due to the small sample size. However, in a meta-analysis, Moraska and colleagues [15] found that eight of nine studies showed immediately decreased salivary cortisol levels after the first massage session. After several massage sessions, though, only five of nine studies reported decreased cortisol levels. In another meta-analysis [16] decrease in cortisol was found to be non-significant. Concerning blood pressure (BP), some studies report no change (e.g. [17]), while some indicate a decrease in systolic pressure (e.g. [18]) and others also reveal a decrease in diastolic pressure (e.g. [19]). In our pre-testing of massage on patients with stroke, we detected a decrease in systolic BP. Using heart rate variability (HRV), which reflects activity in the autonomic nervous system, we have previously found a decrease in sympathetic nervous activity with a subsequent compensatory decrease in parasympathetic nervous activity in healthy individuals receiving massage [20]. This, however, contrasts with other findings of an increase in parasympathetic activity during massage (e.g. [21]). Taken together, this presents a disparate picture regarding the physiological response to massage and more research is needed.

The second part of this project focuses on activity as another component of health in ICF. Sensorimotor function deficits are common after stroke, and depending on the lesions’ location and extent, the frequency of deficits will vary. Somatosensory deficits may cause difficulty managing daily living and prevent rehabilitation [22, 23]. In training somatosensory function after stroke, both improved sensory and motor function have been found [23]. Further, if somatosensory information is suppressed in healthy people, motor function is found to be impaired [24]. Thus, there appears to be strong support for the integration of sensory and motor function. There are both active and passive treatments related to sensorimotor function. Examples of active training are mirror therapy, repetitive sensory discrimination tasks, and sensory recognition training [22]. Other studies evaluate a more passive form of treatment and focus on sensory stimulation by electric stimulation, thermal stimulation, compression, magnetic stimulation [22] or acupuncture [25]. Thus, even if single studies report positive results, as the authors in a Cochrane review [22] conclude, there is insufficient evidence regarding the effectiveness of treatment for sensory loss after stroke, and more studies are needed. Some studies have reported that touch stimulation improves neurological development in children [26]. In the elderly, passive tactile stimulation has been shown to enhance tactile acuity, increase haptic object exploration skills and fine motor function [27]. Pre-clinical studies have shown that touch increased dendrite length and motor function [28], as well as increased neural activity and reperfusion in the involved area [29] in rats after stroke. One study of humans reported that mechanical touch influenced motor function after stroke [30] and thereby sensory stimulation is supposed to increase motor function recovery. Further, combining somatosensory and motor training post stroke (after 6 months or later) has been found to increase fine motor function, sensory discrimination, and musculoskeletal performance [31]. The increased function remained at follow-up three months later. To our knowledge, no study has investigated the effects of TM on stroke patients, although clinical experience shows that TM influences experiences of increased sensory function after stroke.

Stroke causes neurological deficits and it is therefore important to find interventions during the rehabilitation phase that can regain the patient’s abilities and promote neuronal recovery or compensation. Grefkes & Flink [32] argue that recovery from stroke is driven by neuronal reorganization in the brain. Studies using fMRI show that movements in the paretic limb induce abnormal activity in motor-related areas (both contralesional and ipsilesional hemispheres) compared to more focused activity in motor-related areas (contralateral hemisphere) in healthy controls. Furthermore, longitudinal studies have found that in subjects with good recovery, abnormal activity in motor-related areas is decreased and reaches levels similar to those found in healthy controls [32]. Some studies have evaluated brain activity in relation to motor rehabilitation after stroke [33]. The findings showed that in those who successful recovered following treatment, there was a shift from brain activity mainly in the contralesional motor cortex to activity mainly in the ipsilesional motor cortex when activating the affected limb. Also, stimulation of other senses after stroke, like visual stimulation by mirror therapy, affected the reorganization of brain activity toward the ipsilesional hemisphere [34]. The group participating in mirror therapy also improved according to the Fugl-Meyer motor assessment [34]. Results from the aforementioned studies suggest that successful treatment may normalize brain activity. However, as far as we know, no study has evaluated recovery after somatosensory stimulation by TM with respect to brain activity in stroke patients. It has been found, however, that sensory stimulation in stroke patients increase motor recovery, although the mechanisms are unknown [23].

Despite the often high quality of stroke care, decreased general health and independence are frequent in stroke survivors, and there is a need to further improve treatment and rehabilitation. Based on earlier research there are reasons to believe that TM may decrease anxiety, pain, stress reactions, and effect sensorimotor function after stroke and thus has the potential to improve everyday life after stroke. There is therefore reason to further evaluate the effects of TM after stroke.

### Aim, hypotheses and primary and secondary outcomes

This study will evaluate possible effects of TM after stroke on health in the ICF domains. Specific purposes are to investigate the impact on: Body function by means ofAnxietyPainStress reactions
 Activities by means ofSensorimotor functionDisability
 Participation by means ofHealth-related quality of life

Our hypotheses are that TM after stroke will;decrease anxiety and pain (hypothesis I)decrease physiological stress responses (hypothesis II)increase sensorimotor function, which will be reflected in improved gross and fine motor skills and touch discrimination (hypothesis III)increase ability to perform activities in daily life (hypothesis IV)increase activity in contralateral sensorimotor areas and decrease redundant brain activity in motor-related areas. This will lead to more focused activity in motor-related areas, thus improving behavioural movement in the patients (hypothesis V)increase health-related quality of life (HRQoL) (hypothesis VI)

The primary outcome is change in anxiety measured by STAI. The secondary outcomes include pain, physiological stress responses by change in heart rate variability and salivary cortisol, gross and fine motor skills, grip strength, touch discrimination, quality in motor performance, activities in daily life, brain activity, and HRQoL (Table 1).

**Table 1 Tab1:** Outcome assessments in relation to hypothesis and assessment methods

Outcome area	Hypothesis	Outcome	Assessment method
Body function	Hypothesis I	Anxiety (primary endpoint)	The State-Trait Anxiety Scale, (STAI)
		Pain, intensity	VAS
	Hypothesis II	Heart rate variability	ECG
		Salivary cortisol	
		Blood pressure	
Activities	Hypothesis III	Touch discrimination (sensory skills)	Shape Texture Identification Test (STI)
		Gross dexterity (motor skills)	Box and Blocks
		Fine motor dexterity (motor skills)	Nine Hole Peg
		Grip strength (motor skills)	Jamar® Hydraulic Hand Dynamometer
	(Subsample II)	Quality in motor performance	High-speed cameras in Movement laboratory
	Hypothesis IV	Disability after stroke	Modified Rankin Scale, Barthel index
	Hypothesis V (subsample 1)	Brain activity during finger-tapping/movement	GE 3 T scanner (General Electric, USA).
Participation	Hypothesis VI	Health-related quality of life	Nottingham Health Profile (NHP)

## Methods

### Design

This project is a prospective randomized open-labelled control trial with blinded evaluation (PROBE-design) of TM after stroke. Minimization will be used to create groups for intervention and control. Using minimization offers a way to stratify groups and ensure balance with respect to significant variables also in smaller samples. Minimization is considered to have an advantage in small trials (cf. [35]) and is an acceptable alternative to random assignment according to the CONSORT statement (http://www.consort-statement.org) and SPIRIT checklist (http://www.spirit-statement.org/spirit-statement/).

## Participants

### Participants

#### Inclusion criteria

Fifty participants will be recruited from two stroke units in northern Sweden within one week after the onset of stroke. The inclusion criteria will be 1) acute stroke defined according to the WHO-criteria of a neurological deficit of cerebrovascular cause that persists beyond 24 h [36]. The stroke cases are classified according to the TOAST (Trial of Org 10172 in Acute Stroke Treatment) [37] and OCSP (Oxford Community Stroke Project) [38] systems, 2) impaired finger tapping on the affected side of the body, 3) visible volitional flexion of the fingers on affected side of the body.

#### Exclusion criteria

Individuals with 1) cancer, 2) infections with fever, 3) psychiatric and 4) neurologic diseases and 5) alcohol or drug addiction may have affected general condition that will complicate interpretation of outcomes and will be excluded. 6) Conditions that impede communication can hamper the possibility to receive information and assess outcomes, therefore those individuals will also be excluded. A research nurse will collect information from the patients and staff concerning inclusion and exclusion criteria.

#### Power analysis and group distribution

In all, this study will include a total of 50 participants with 25 participants in each group. The power analysis is based on the primary outcome anxiety assessed with the State-Trait Anxiety Inventory (STAI) instrument (total score 20 – 80). Based on results from a previous study [1], the assumption is to find a difference in score corresponding to 8. Twelve subjects in each group will have an 80 % probability of achieving a statistically significant difference at a 5 % level. The subjects are allocated to the groups consecutively and by using minimization the groups are balanced with respect to severity in anxiety assessed with State-trait Anxiety Inventory (STAI) [39] and disability assessed with a Modified Rankin Scale (mRS).

Sub-sample I will consist of 30 participants (15 from the intervention group and 15 from the control group) who will be invited to participate in an fMRI study to evaluate brain activity during motor task performance. The inclusion criteria will be unilateral hemispheric stroke, intracerebral ischemic or hemorrhage lesion, first-ever stroke and cortical and/or subcortical lesions verified by radiology and/or clinical diagnosis, and fulfill the criteria for fMRI used at the Umeå Center for Functional Brain Imaging (UFBI), Umea University. An earlier study [40] found that the sample is adequate to produce stable and replicable results.

For feasibility purposes, a sub-sample (II) of 10 participants will be tested for dexterity in a movement laboratory before and after intervention.

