### Recruitment procedure

A research nurse at the stroke unit will monitor admitted patients via patient records according to the inclusion and exclusion criteria and together with a stroke physician decide whether the patient is suitable or not. With a computer program the stroke physician will allocate the participant to one of the two groups and report group affiliation to the massage therapist. The massage therapist will give the patient oral and written information about the study and informed consent will be obtained.

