### Data analysis

Data will be analyzed with repeated measurement methods to compare the intervention group and the control group. Statistical regression models that adjust for background characteristics and account for correlated measurements for the same individual will also be used (e.g., mixed effects model and generalized estimating equations). Data will be analyzed by inter-group analyses using the Statistical Package for Social Science (SPSS). Effect size will be estimated with Cohen’s d. The analysis will be performed on an intention-to-treat basis.

HRV will be analyzed by automatic detection of heartbeats, then the R-R interval data will be derived and transformed into an evenly sampled heart rate time series. From this time series HRV will be analysed in the frequency domain where the relative influence of different spectral components will be determined. From the signal, the mean heart rate, the total spectral power (PTOT), and the power of the low-frequency (PLF; 0.04-0.15 Hz) and high-frequency (PHF; 0.15-0.40 Hz) will be calculated. The recording and analysis software has been developed at Department of Biomedical Engineering (DBE), Vasterbottens county council (VLL) and will be analysed in collaboration with DBE, VLL.

The fMRI data will be analyzed in collaboration with experts at the UFBI. The effects of TM on sensorimotor functions and brain activity over time will be studied and compared within and between the intervention and control groups. The analysis will be similar to an earlier fMRI study [56].

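### As written, entry to the fMRI sub-sample can depend on the allocated arm, and within-arm change cannot test hypothesis V

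*Protocol article*

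**What the plan says.** The section Power analysis and group distribution sets the fMRI sample by arm: "Sub-sample I will consist of 30 participants (15 from the intervention group and 15 from the control group) who will be invited". It adds eligibility criteria beyond those of the main trial: "The inclusion criteria will be unilateral hemispheric stroke, intracerebral ischemic or hemorrhage lesion, first-ever stroke and cortical and/or subcortical lesions verified by radiology", plus suitability for the scanner. The size is justified by one sentence: "An earlier study [40] found that the sample is adequate to produce stable and replicable results".

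For the trial as a whole, the same section states that "by using minimization the groups are balanced with respect to severity in anxiety assessed with State-trait Anxiety Inventory (STAI") and for disability on the mRS. No other minimisation factor is named.

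Recruitment procedure gives the order of events. First, "With a computer program the stroke physician will allocate the participant to one of the two groups and report group affiliation to the massage therapist". Then, "The massage therapist will give the patient oral and written information about the study and informed consent will be obtained". The article describes no separate procedure for the fMRI invitation.

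The Assessments section places the scans at BL and W2. Data analysis says that brain activity over time will be "compared within and between the intervention and control groups".

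**The concern.** A sub-sample keeps the protection of the allocation if membership is fixed before allocation, or afterwards by a rule that cannot respond to the arm. The article describes neither. It fills a fixed number from each allocated group by invitation, and the recruitment sequence makes the arm known to the therapist before consent. If staff approach TM and sham patients differently, or if patients in the two groups differ in willingness to be scanned, the two sets of 15 may differ in prognosis. A fixed quota can also hide this, because inviting continues in the slower arm until the numbers match.

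The within-arm comparison raises a second problem. Hypothesis V predicts that TM will make motor-related activity more focused. The Background reports that abnormal activity in these areas subsides in patients who recover well. Treatment starts one week after onset, and the second scan follows the two-week course. Some change in that direction is therefore to be expected without TM.

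At stake is hypothesis V, one of six. Its only evidence comes from this sub-sample.

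**Working it through.** **1. Who can enter, and when.** Setting the sections side by side:

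- The quota refers to the intervention and control groups. These exist only after allocation, so filling 15 places in each requires someone who knows the arm.
- In Recruitment procedure, allocation and disclosure to the therapist come before information and consent. No section places any consent earlier.
- With 25 patients per arm and 15 places, 25 − 15 = 10 per arm (10/25 = 40%) are not scanned. They may be ineligible, decline, or not be chosen. The article gives no rule for choosing if more than 15 qualify. There is thus room for selection, although its direction and size cannot be computed from the document.

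**2. What minimisation covers.** The factors are STAI and mRS, applied to all 50. fMRI participation is not a factor. Balance among the 50 does not carry over to 30 chosen after allocation if the choice can depend on the arm.

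**3. What the within-arm comparison can show.** Write the mean BL-to-W2 change as R + T in the TM arm and R in the control arm, where R is recovery under ordinary care plus the effect of attention and T is the specific effect of TM. The within-TM change estimates R + T. Only the difference between arms, (R + T) − R = T, addresses hypothesis V. That subtraction is valid only if R is the same in both sets of 15, which is the condition that step 1 leaves unprotected.

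**4. Precision with 15 per arm.** The article gives no effect size, SD, alpha or power for the fMRI sample, so there is no stated figure to reproduce. The calculations below use 80% power and a two-sided 5% level.

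- Normal approximation, W2 values alone: d = (1.960 + 0.842) × √(2/15) = 1.02.
- Noncentral t, 28 degrees of freedom, noncentrality d√(15/2): d = 1.06.
- Power of the same t test: 26% at d = 0.5, 56% at d = 0.8 and 75% at d = 1.0.
- Adjusting W2 for BL multiplies the detectable difference by √(1 − r²), where r is the BL–W2 correlation. The small loss of a degree of freedom is ignored. The document gives no r, so a range is assumed:

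| Assumed r | √(1 − r²) | Detectable difference (SD of W2 activity) |
|---|---|---|
| 0 | 1.000 | 1.06 |
| 0.5 | 0.866 | 0.92 |
| 0.7 | 0.714 | 0.76 |
| 0.8 | 0.600 | 0.64 |

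- Stricter levels for several brain regions (assumed) work the other way. Unadjusted, the detectable difference is 1.33 SD at alpha 0.01 and 1.67 SD at alpha 0.001. With r = 0.8 these become 1.33 × 0.6 = 0.80 and 1.67 × 0.6 = 1.00.

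A difference of 0.5 SD stays below 80% power throughout this range.

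**The case against.** The strongest reply is that arm-aware invitation to fMRI is inferred. The article does not say who invites, when, or how patients are chosen, and 15 + 15 could simply describe what 1:1 allocation is expected to yield. A condensed article may leave such detail to the full protocol. This stands in part: the inference is strong, because the quota wording and the recruitment sequence agree and nothing points the other way, but it is not an express statement. Nor does the document say that patients know their arm when they are invited.

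Several stronger readings are tempting and are not supported:

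- *The stricter criteria break the allocation.* They are baseline features. Applied alike in both arms, they narrow the population and leave the comparison intact.
- *The adequacy sentence is a wrong power claim.* It speaks of stable and replicable results and claims no power. No stated figure is shown to be wrong, and a secondary sub-sample need not be powered.
- *Only very large differences are detectable.* The 1.06 SD applies to an unadjusted test. BL scans are planned, and adjusting for them lowers it.
- *Hypothesis V will be judged on the TM arm alone.* The plan names between-arm comparison too, and Data analysis refers generally to inter-group analyses. The weakness is that the two comparisons stand together without one being given precedence.
- *The quota is unreachable.* It needs 30/50 = 60% of patients, but the document gives no eligibility or agreement rate against which to judge that.

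Two further replies have weight. The first scan is at BL, so entry cannot depend on response to the two-week course. Consent after allocation also concerns all 50 patients, not just these 30. Moving main-trial consent earlier would remove part of the threat here, but an fMRI invitation made by arm after allocation would remain.

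**Conclusion.** The point holds in a limited form. As written, invitation, selection and agreement to fMRI can depend on the arm, and minimisation of the 50 does not protect the comparison of the 30. This rests on reading the per-arm quota together with the order in Recruitment procedure. The possible bias cannot be sized from the document, and no imbalance is shown. Separately, and without that inference, within-arm change cannot support hypothesis V, because the Background itself describes a similar change in patients who recover well.

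The sub-sample suits an exploratory comparison. Its detectable difference is about 1.06 SD unadjusted and about 0.92 to 0.64 SD with BL adjustment, given the assumed correlations of 0.5 to 0.8, and larger under multiplicity control. The primary STAI comparison does not rest on this sub-sample. This is an inexpensive improvement to a secondary part of the trial and does not put the main design in doubt.

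**What to change.** 1. Check fMRI eligibility and obtain fMRI consent before allocation, and make no invitation by arm. Minimisation on STAI already needs a score from the patient before allocation, so there is a point of contact at which to do this. Optionally, add fMRI participation (yes/no) as a minimisation factor, so that a split near 15/15 arises without a quota.
2. In Data analysis, state that the conclusion on hypothesis V rests only on the between-arm difference in W2 activity adjusted for BL, that within-arm changes are descriptive, and that the fMRI comparison is exploratory.
3. If a precision statement is added beside the adequacy sentence, give both the unadjusted figure (about 1.06 SD) and the adjusted range (about 0.92 to 0.64 SD at assumed correlations of 0.5 to 0.8), and note that multiplicity control raises them.

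The cost is slightly earlier fMRI screening inside the one-week recruitment window, possibly one more minimisation factor, some rewording, and a final split that may not be exactly 15/15. No additional scans are needed.
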